### ***Current practices of BC MPV testing in Norway***

Current criteria for MPV testing are characterized here:

<https://www.helsebiblioteket.no/retningslinjer/brystkreft/forord>

Criteria for genetic testing of BC patients:

- Women diagnosed with BC 60 years or younger.
- Male BC any age.
- Women diagnosed with ovarian cancer at any age.
- Women diagnosed with BC older than 60 years with a family history of cancer as follows:

1) One first-degree relative (or second-degree through a man) with BC, and the mean age of onset is 55 years or younger.

2) Two first-degree relatives (or second-degree through a man) with BC at any age.

3) One first-degree relative (or second-degree through a man) with ovarian cancer.

4) One first-degree relative with prostate cancer 55 years or younger.

A healthy woman can be offered genetic testing if she has a first-degree relative who fulfills any of the criteria above.

### Follow up of women with an increased familial risk for BC:

Women with a mutation in the high-penetrance genes are offered risk-reducing surgery with prophylactic mastectomy. High-risk women who have not removed their breasts are offered annual screening with mammography and breast MRI from the age of 25 until the age of 70 for women with BI-RADS density category c or d, and 60 for women with a density a or b. Above this age (60/70), the women are offered annual mammography as long as considered appropriate according to general health status.

Women considered to have an increased familial risk for BC without mutations in the high-penetrance genes are recommended annual mammography from 40-60 years. From the age of 50, they are screened every second year in the ordinary screening program and referred for clinical mammography the years

in-between. From the age of 60, they are recommended to participate in the ordinary biennial screening program. No special follow-up is recommended after the age of 70.

### ***Polygenic risk score***

A considerable part of BC variation is explained by variants outside these high-risk genes in the form of BC-associated common single-nucleotide polymorphisms (SNPs) (22).

**A polygenic risk score (PRS)** is the combined effect of individual breast cancer susceptibility variants identified by genome-wide association studies. Although individual associated SNPs may confer only modest disease risk, the combined effect of all known associated SNPs on risk can be substantial. Under the assumption of a simple multiplicative model, the collection of known susceptibility SNPs for any given trait or disease can be combined into a risk profile that can be used for risk prediction.

Several studies have combined SNPs with genome-wide significance into a summary estimate of BC risk using a PRS approach (23, 29, 30). Initial attempts by Mavaddat et al. (23) and Sieh et al. (31) demonstrated a strong effect of the score in predicting future BC cases. Other major efforts such as those by Mavaddat et al., Khera et al., and Hughes et al. additionally elucidated the use of PRS as a BC predictor (29, 32, 33).

BC PRS tests are not yet widely implemented in healthcare.

### ***Polygenic Risk Score (PRS) test AnteBC***

AnteBC is a genetic test that assesses a woman's personalized risk of developing breast cancer (BC) using a polygenic risk score (PRS).

Health technology company Antegenes (License number L04685) has developed AnteBC as a laboratory test. AnteBC is registered as a medical device (IVD) in Estonian Medical Devices Database (EMDDDB code: 14726).

For the PRS calculation, AnteBC uses the patient's DNA data from genotyping. Genotyping is performed using the AnteBC test with a non-invasive saliva-based method to collect and isolate a patient's DNA. The standard procedure includes the use of Illumina Global Screening Array-24 (GSA) v3.0 chip and Illumina iSCAN sequencer for genotyping. This workflow genotypes the ~762 000 markers on the GSA chip by following the Illumina Infinium HTS (high-throughput screening) protocol (Illumina Inc, <http://www.illumina.com>; Document # 15045738 v04).

The test can also use information from other microarrays and sequencing approaches that output DNA data broadly covering the human genome.

Antegenes performs the risk assessment based on imputed genotype data. Quality-controlled markers resulting from genotyping are imputed using a 1000G panel with reference to the human genome GRCh37.

### **Aim of the AnteBC test**

The purpose of the AnteBC test is to reduce the risk of premature mortality due to BC through stratified precision BC screening and other preventive measures. AnteBC is a tool for individual BC risk estimation, which is the basis for more precise and efficient prevention. The aim is to evaluate the genetic

predisposition for BC with PRS technology (AnteBC test) and detect women with moderately or highly raised BC risk for stratified screening.

#### AnteBC clinical indications

Target population: AnteBC test is recommended for women between the ages of 30 and 75 of primarily European ancestry, but the test has also corrections for other ethnicities based on analyses of risk performance with UK Biobank ethnic groups' data.

### **BC risk prediction models**

The classical BC risk prediction models provide risk estimates by either non-genetic risk factors (demographics, reproductive history, menopausal status, family history, breast biopsies, and mammographic density) (34, 35) or by penetrance data from high-risk families with BRCA1 and BRCA2 mutations (36, 37).

**QCANCER** (<http://www.qcancer.org/female/index.php>) requires age, smoking, alcohol consumption, familial history of various cancers, other diseases (T2D, COPD), etc. This and other non-genetic models have a limited utility on large scale, as up-to-date information about risk factors is not available. QCancer® has been developed for the UK population and is intended for use in the UK.

The **Claus model** includes first- and second-degree relatives with breast and/or ovarian cancer, and incorporates the age at diagnosis (38). Among the limitations of the Claus model are that it applies only to women with a family history of BC and does not consider nonhereditary risk factors. In addition, the Claus model can calculate risk for only up to two relatives with BC.

The **BRCAT or Gail model** (<https://www.cancer.gov/bcrisktool/>) is primarily focused on personal risk factors for BC and estimates the patient's five-year and lifetime risk of BC. The five-year risk can be used for chemoprevention recommendations if the risk is greater than 1.67 percent. The main limitation of the Gail model is that it includes only first-degree relatives, which underestimates the risk in women with BC history in their paternal lineage. The Gail model also does not consider the age of onset of BC. These risk calculations have been validated for women in the U.S. who are screened regularly for BC.

The **BRCAPro** (<http://bcb.dfci.harvard.edu/bayesmendel/brcapro.php>) (39) considers a patient's age, the age of first- and second-degree relatives and their breast and ovarian cancer status, along with *BRCA1* and *BRCA2* mutation frequencies and cancer penetrance. The patient's ethnicity and age at which she has had a salpingo-oophorectomy (the removal of the ovaries and Fallopian tubes) are also components of the BRCAPRO risk calculation. This model does not consider nonhereditary risk factors.

The **Breast Cancer Surveillance Consortium (BCSC)** model (<https://tools.bccsc-scc.org/BC5yearRisk/intro.htm>) was developed and validated in 1.1 million women undergoing mammography across the United States, among whom 18,000 were diagnosed with invasive breast cancer (40).

The **BOADICEA** (the Breast and Ovarian Analysis of Disease Incidence and Carrier Estimation Algorithm) (<http://ccge.medschl.cam.ac.uk/boadicea/>) (41, 42) is a comprehensive model that can be used to calculate the future risks of developing breast or ovarian cancer using the information on family history, lifestyle/hormonal risk factors, rare pathogenic variants in moderate and high-risk breast/ovarian cancer

susceptibility genes, common breast/ovarian cancer genetic susceptibility variants (PRS) and mammographic density. It can also be used to calculate the likelihood of carrying mutations in the moderate to high-risk genes BRCA1, BRCA2, PALB2, ATM, CHEK2, BARD1, RAD51C, and RAD51D (43).

The **CanRisk Web Tool** incorporates the new version of BOADICEA v8, the Breast and Ovarian Analysis of Disease Incidence and Carrier Estimation Algorithm. <https://www.canrisk.org>

The **Tyrer-Cuzick model** (the International BC Intervention Study [IBIS]) (<http://www.ems-trials.org/riskevaluator/>) (44) considers the patient's age; BMI; age at first menstrual period; age at first live birth; age at menopause; hormone replacement therapy use; breast biopsies; atypical ductal hyperplasia; lobular carcinoma in situ; and family history of breast and ovarian cancer in first- and second-degree relatives. This model also estimates the risk for the presence of a non-*BRCA1/BRCA2* BC susceptibility gene mutation. The program assumes that there is a gene predisposing to BC in addition to the *BRCA1/2* genes. The risk from other classical factors including age at a first child and benign disease is combined with familial risk.

For risk-based screening, combined risk models must be easily accessible and user-friendly, but as medical devices for medical decisions according to European Union regulations, they should be compliant with relevant healthcare regulations. The practical routine application of such compounded models has been complicated due to the non-availability and quality of data about individual risk factors. In practical settings, the data collection difficulties need to be weighed with expected gains.

### 3.5. BC Risk Categories

The first step in determining a risk category is to assess for major risk factors to identify women at average risk, which is the category for most women and to identify the smaller number of women at moderate or high risk of developing BC. The risk categories are delineated according to the lifetime risk of being diagnosed with BC (not according to the risk of dying due to BC). There is no standardization or consensus about the exact percentages of lifetime risk of developing BC within each risk category.

Major factors used to determine a risk category, based on a patient's history, are:

- Personal history of ovarian, peritoneal (including tubal), or BC.
- Family history of breast, ovarian, or peritoneal cancer.
- Genetic predisposition (if the patient's *BRCA* or another genetic marker status is known).

Women who have none of these risk factors are usually considered at average risk. Most women are in this average-risk category, with an average lifetime risk of being diagnosed with BC estimated at 12.4 percent in the USA population.

The study by Maas et al. estimated the average absolute risk for a 30-year-old white woman in the United States to develop invasive breast cancer by the age of 80 years at 11.3% (45). A model that includes all risk factors provided a range of average absolute risk from 4.4% to 23.5% for women in the bottom and top deciles of the risk distribution, respectively. For women who were at the lowest and highest deciles of nonmodifiable risks, the 5th and 95th percentile range of the risk distribution associated with 4 modifiable factors were 2.9% to 5.0% and 15.5% to 25.0%, respectively. The percentage of the population could be divided to be of moderate risk (twofold to threefold risk

compared with the population average) and high risk (above threefold risk compared with the population average).

In the review by D. Easton et al. risk levels are defined as: moderate risk as a risk of breast cancer, defined in terms of disease incidence, that is two to four times as high as that in the general population, and high risk as an incidence that is more than four times as high (46).

In the WISDOM study for women aged 40 to 49 years, screening is recommended when their five-year risk equals or exceeds that of the average woman aged 50 years (47). They based thresholds on five-year risk given that screening and prevention are most impactful in those at immediate risk of cancer, and five-year risk thresholds are standardly used to guide chemoprevention. The 5-year risk estimate in the WISDOM study for women aged 50 was 1.3%.

UK National Institute for Health and Care Excellence (NICE) guidelines for the management of familial BC define BC risk categories using the following thresholds (48), Table 8 below:

**Table: BC risk categories by NICE guidelines**

|                             | BC risk category     |                                  |                 |
|-----------------------------|----------------------|----------------------------------|-----------------|
|                             | Near population risk | Moderate risk                    | High risk       |
| Lifetime risk from age 20   | Less than 17%        | 17% or greater but less than 30% | 30% or greater  |
| Risk between ages 40 and 50 | Less than 3 %        | 3-8%                             | Greater than 8% |

Also, the following approach has been used: generally, they are as follows: average (less than 15 percent), moderate (approximately 15 to 20 percent), or high (greater than 20 percent) lifetime risk.

**PRS methodology** uses the normal statistical distribution of risks, therefore PRS risks distribution has no clear different thresholds. For the clinical implementation of the PRS test, Antegenes has developed clinical recommendations using based mostly on two aspects – the average BC risk level currently accepted for routine BC public screening and the analogy with clinical recommendations for moderate-risk MPV carriers(49)(50). For risk-based recommendations based on the PRS, it is possible to divide the patient's relative risk of developing BC into different levels compared to the average in the given age, while accurately assessing the risk of a particular percentile. In Europe, mammography screening in the age group 50-69 years at two-year intervals is currently a recognized standard practice, which reduces BC mortality. Consequently, the “zero point” of the risk level at the beginning of the screening is the average risk level of 50-year-old women. Detecting younger women with similar or higher risk levels already from age 30-to 35 allows implementing for them similar mortality reduction measures, avoiding same time screening measures for women with lower risk. In the case of different standard-screening groups (for example, screening from age 40), it is possible to apply accordingly modified recommendations. As PRS can predict similar BC risk levels to moderate risk MPVs (in genes *ATM*, *CHEK2*, and others), we used for our recommendations analogy with these for mammography intervals and magnet resonance imaging use(49)(50).

### 3.6. Cost-effectiveness data of personalized risk-based screening

Simulation models have suggested that tailoring screening based on individual risk factor profiles may be more cost-effective than uniform screening (10) and using genetic risk thresholds rather than age may more efficiently identify candidates for screening (50). A systematic review with a focus on the cost-effectiveness of risk-adapted strategies concludes that e that BC screening and prevention are cost-effective in the European settings (51). All screening models predict gains in life expectancy, which has not yet been confirmed by trials with long follow-up periods. European models evaluating risk-adapted screening strategies are rare but suggest that risk-adapted screening is more effective and cost-effective than conventional screening (51).

### 3.7. Background Summary and Study Rationale

The current 'one-size-fits-all' BC screening approach does not consider individual risks of women and there is a need for more precise screening which considers individual risks of women.

BC screening is widely implemented in many healthcare systems to reduce BC mortality through earlier diagnosis. Also, in Norway screening is offered to women in age 50-69 with mammography after every 2 years. Screening with mammography reduces BC mortality risk 20-40% among women at age 50-69. But approximately 20% of BCs occur in women younger than 50 years. The relationship between benefits and potential harms for screening in the age group under 50 years has been controversial and, in most countries, as well as in Norway, screening is not offered in this risk group.

For a personalized approach, we need tools for risk stratification. Around 30% of the total BC risk has been shown as hereditary, therefore genetic predisposition tests serve as tools for risk estimations. These tools are already in clinical use in the form of polygenic risk score (PRS) tests and monogenic pathogenic variants' (MPV) tests, and these can serve as BC risk prediction instruments for personalized prevention. Also, BD in mammography is a tool for BC risk prediction and more precise recommendations for screening. We have developed a new model for a genetic risk-based BC screening program that enables personalized prevention based on individual risk levels.

The screening plan should depend on a woman's risk for BC and personal preferences. The use of genetic risk scores and mammographic BD identifies women that are at increased risk of developing the disease.

Risk assessment per se does not have inherent clinical utility; the subsequent adoption of a risk-based intervention based on the results of the assessment is what influences the health outcomes. The use of such a strategy depends on whether the risk-based intervention is appropriate, accessible, practicable, and acceptable. To combine individual genetic risk testing, BD information and subsequent healthcare services, it is necessary to create and implement a whole program of personalized genetics-based BC screening and prevention. It is necessary to evaluate: the benefit-harm trade-offs of such strategies and the acceptability and feasibility of implementing risk-stratified prevention and early detection programs.

The current project is aimed to investigate these aspects as a comprehensive program of personalized BC prevention and screening.

#### Key hypotheses:

- Genetics-based BC prevention program has a clinical utility and is cost-effective for women under age 40 or 50.

- Genetics-based BC prevention program is feasible and acceptable, and healthcare systems are ready to implement that.

**Research questions also are:**

- What is the clinical utility and effectiveness of personalized BC screening and prevention?
- What is the cost-effectiveness of genetics-based personalized precision prevention?
- Is genetics-based personalized precision prevention feasible in clinical practice?
- What are the acceptability, values, preferences, and social norms for personalized precision prevention?
- Is the accessibility of genetics-based personalized precision prevention equitable?
- How ready are the healthcare systems for the implementation of personalized precision prevention as a population-based approach?

#### **4. OBJECTIVES AND OUTCOME MEASURES**

The general aim is to perform a clinical cohort study that would test issues regarding the deployment of PRS test AnteBC and MPV-based risk testing in the Norwegian clinical setting. This clinical pilot would simultaneously evaluate logistical and ethical considerations (patient risks, feedback, operational procedures), test the flow of information, and would also create prospective performance data for PRS testing. In addition, the project will explore the relationship between PRS and mammographic density (MD).

The target group is healthy women at age 40-49, which is the age group before the current official screening. For genetic risk prediction, the project uses PRS and, if indicated, MPV tests as healthcare services with the following diagnostic screening and prevention activities.

**Primary aim:**

To evaluate the impact of implementing population-based genetics testing strategy for BC precision prevention using the PRS and MPV testing.

**Measurable primary outcome:**

Elevated-risk BC PRS and MPVs prevalence for precision screening - the proportion of women with elevated risk for personalized screening.

The proportion of women detected with higher genetic or breast density risk for BC screening according to:

- PRS risk.
- Monogenic risk.
- Based on high BD on mammography.

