## **5. STUDY DESIGN**

General population-based cohort study combined with modelling studies.

The target number of study participants: 80.

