#### **Exclusion Criteria:**

- Women with already diagnosed malignancies or hereditary cancer syndromes.
- Signs of malignancy after mammographic assessment.
- Women already tested for MPVs and PRSs.
- Ashkenazy Jewish ethnicity.

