## **STEP 2. Genetic testing / Risk evaluation**

A recommendation on the level of the genetic test is given, variants:

- All women: PRS testing. Genotyping is performed using the AnteBC test with a non-invasive saliva-based method to collect and isolate a patient's DNA. Antegenes performs the risk assessment based on imputed genotype data.
- In addition: questionnaire about genetic and cancer family history.
- Women that fulfill standard criteria according to national guidelines will be submitted to genetic counselling and testing of monogenic germline pathogenic variants (MPV), see chapter 3.2 for criteria.

After the patient's **informed consent**, an AnteBC test is performed and, if indicated, a patient is directed also for **MPV testing**.

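### The primary outcome is called MPV prevalence, but MPV testing restricted to women meeting national criteria can give only a detection yield

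*Protocol*

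**What the plan says.** The primary aim (Section 4) is "To evaluate the impact of implementing population-based genetics testing strategy for BC precision prevention using the PRS and MPV testing". The measurable primary outcome in the same section, repeated in the Synopsis, is "Elevated-risk BC PRS and MPVs prevalence for precision screening", explained there as the share of women whose raised risk would call for tailored screening. A second sentence describes it as "The proportion of women detected with higher genetic or breast density risk for BC screening according to" three components: PRS, monogenic risk and high breast density.

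Section 5.2, Step 2, gives PRS testing to all women. For MPVs it says: "Women that fulfill standard criteria according to national guidelines will be submitted to genetic counselling and testing of monogenic germline pathogenic variants (MPV". Section 4 likewise makes MPV testing conditional on an indication. The national criteria are set out in Section 3.4 under current Norwegian MPV testing practice (Step 2 points to chapter 3.2). They allow testing of a healthy woman when a first-degree relative meets one of the listed conditions.

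The exclusion criteria in Section 5.1 include "Women with already diagnosed malignancies or hereditary cancer syndromes" and "Women already tested for MPVs and PRSs".

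On size, Section 5 says only "The target number of study participants: 80". Section 6.1 plans mainly descriptive statistics. No denominator is given for the monogenic component, and nothing says how an untested woman is counted.

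**The concern.** A prevalence needs the carrier status of everyone in the group it describes, or of a representative sample of them. Here status is found only in women selected for a family history that raises the chance of carriage. For all others it is unknown, which is not the same as negative. The MPV recommendations in Step 3 have one branch for an MPV detected and one for none detected, but none for a woman not tested. Section 5.4 collects MPV results and family history but has no separate item for meeting the criteria or for being tested. Nothing therefore prevents untested women from being counted as non-carriers.

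At stake is what the primary outcome can support. Section 4 says the cost-effectiveness model will take input data from the pilot. A criteria-based yield entered there as a prevalence would misstate what population-wide MPV testing would find.

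**Working it through.** **1. Is there a figure to reproduce?** No. The target of 80 has no derivation, expected prevalence or precision goal, and no MPV rate or testing share is given. The check is one of logic, followed by illustration under stated assumptions.

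**2. Who is observed for each genetic component?**

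| Component | Assessed in | Source |
|---|---|---|
| PRS | all enrolled women | Section 5.2, Step 2 |
| MPV | women meeting national criteria | Section 4; Section 5.2, Step 2 |

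**3. What each denominator estimates.** Let f be the share meeting the criteria (all assumed tested), π1 MPV carriage in those women and π0 carriage in the rest.

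- True prevalence in the enrolled group: f·π1 + (1 − f)·π0.
- Expected MPVs over all enrolled: f·π1. The term (1 − f)·π0 is lost.
- Expected MPVs over tested women: π1. This exceeds the true value whenever π1 > π0.

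**4. Illustration.** f, π1 and π0 are assumptions. With f = 15%, π1 = 5%, π0 = 2%:

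- True: 0.15 × 0.05 + 0.85 × 0.02 = 0.0075 + 0.0170 = 2.45%.
- Over all 80: 0.75%, or 0.75/2.45 = 31% of carriers.
- Over tested women: 5%.
- Chance of no carrier found: (1 − 0.0075)^80 = 55%.

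The range was taken over f = 5% to 30% and the (π0, π1) pairs (1%, 3%), (2%, 5%), (2%, 10%) and (3%, 10%). True prevalence then runs from 1.1% to 5.1%, the expected figure over 80 from 0.15% to 3.0%, and the share of carriers counted from 12% to 68%.

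**5. What the data alone can say.** With t women tested and x carriers found, prevalence among the 80 lies between x/80 and (x + 80 − t)/80. For t = 12 and x = 0, that is 0% to 68/80 = 85%.

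**6. Precision, if an interval were later computed.** With no carriers, the exact 95% (Clopper-Pearson) upper limit is 1 − 0.025^(1/n).

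| n | Upper limit |
|---|---|
| 80 (all enrolled) | 4.5% |
| 16 | 20.6% |
| 12 | 26.5% |
| 8 | 36.9% |
| 4 | 60.2% |

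The rows for 4 to 16 are assumed numbers tested (5% to 20% of 80). The limits refer to different groups: the first row to detections among all enrolled, the others to carriage among women meeting the criteria. The gap shows how little is observed. It does not measure bias.

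**7. Does an interval on x/80 miss the true prevalence?** Not usually when prevalence is low. In the scenarios of step 4 with true prevalence up to 4.4%, it covers the true value in at least 99% of samples. Coverage falls to 91% at 5.1% (f = 30%). With π0 = π1 = 5% it is 18% to 70%, depending on f. The bias in the estimate is therefore the firmer point.

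**The case against.** The strongest reply is that the outcome can be read as a yield. Its second sentence speaks of women detected, and the aim concerns implementing a strategy, which here is PRS for all and MPV testing where indicated. On that reading, MPVs detected over enrolled women is a valid description of those women. This stands, and it points to the remedy: the outcome should say yield, because prevalence claims something else.

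A reader might infer that the protocol will divide by 80 and report a falsely narrow interval. The document does not support that. It never names 80 as the MPV denominator, plans no interval, and may leave both to an analysis plan that is not shown. The precision figures above apply only if someone later puts an interval on x/80, and they depend on an unknown number tested. An analysis plan could not supply the prevalence, however, because neither denominator gives one.

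A reader might also infer that the exclusions remove a known share of carriers. Excluding recognised syndromes fits a target group of healthy women. The exclusion for earlier testing can be read as needing both tests or either one, and if both, women tested only for MPVs stay eligible. The exclusions probably lower the yield, but by an amount that cannot be computed from the protocol.

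Finally, this is a descriptive pilot of 80 women with no test or decision threshold on MPV prevalence. That limits the severity.

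**Conclusion.** The concern holds in this form: the design cannot estimate the MPV prevalence named in the primary outcome. MPVs over all enrolled women probably understate it, and MPVs over tested women describe a group selected on family history. The conclusion needs only the testing rule and the outcome wording, both fixed in the protocol. The sizes shown (for example 0.75% expected against 2.45% true, or 12% to 68% of carriers counted) rest on assumed testing shares and carriage rates and are illustrations.

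It would go too far to say that the whole primary outcome fails or that the planned analysis is falsely precise. The PRS and density components are untouched, and no such interval is planned. Severity is moderate: the change affects what the primary outcome can conclude, but it is one of label, denominator and claim.

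**What to change.** - In the Synopsis and Section 4, replace the MPV prevalence wording with *MPVs detected under national testing criteria (detection yield)*.
- Report number meeting criteria / enrolled, number tested / number meeting criteria, and MPVs / number tested, each with an exact interval. Show MPVs detected / enrolled alongside, labelled as yield.
- State that untested women have unknown MPV status, and that no population MPV prevalence will be inferred or entered as such in the cost-effectiveness model.
- Record for each woman whether she met the criteria and whether she was tested.
- Say whether the prior-testing exclusion means both tests or either, and correct the Step 2 cross-reference to the criteria.

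The cost is protocol wording, two data items and a small table. Who is tested and how women are managed stay as they are. The downside is that the prevalence claim is dropped. Counting women turned away for prior testing or a known syndrome would help interpretation, but it needs a screening log that the protocol does not describe, so it is optional.
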